### Randomization

Randomization will be performed centrally by The Copenhagen Trial Unit. The allocation sequence will be computer-generated and hidden from the investigators and participants. The allocation ratio will be 1:1 and stratification variables will be parity (0 or more), centers (Roskilde or Herlev) and previous larger pelvic surgery (yes/no).

### Blinding

The surgeon operating the patient cannot, for obvious reasons, be blinded. All patients and all caregivers (except the surgeons) at the clinical departments will all be blinded to trial intervention allocation. This is possible because patches on the stomach are placed the same way regardless of conventional or 3D surgery. The medical doctors evaluating the patient condition after surgery and discharging the patients will also be blinded to the trial intervention allocation.

### Outcomes

#### Primary outcomes

The impact of surgery on quality of life, assessed by questionnaire (SF-36-v2, physical health score) at a telephone interview 6 weeks postoperatively.
*Postoperative pain is assessed on a 100 mm VAS-scale immediately after the operation at the admission to post anaesthesia care unit (PACU) and again 5 h postoperatively at gynaecological unit or at the PACU if the patient unexpectedly has not returned to gynaecological unit. These measures are related to the patient lying quiet in the bed. Further pain related to physical movements, will be reported in the morning on day 1–3 postoperatively (longitudinal data). Postoperative pain will also be related to the analgesics given as we register the use of units of morphine during the first 3 days.*

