### Statistical analyses

The statistical analysis plan will be described in detail and published in “BMC Medical Research Methodology”.

Our primary analyses for all outcomes will be adjusted for the three stratification variables (number of previous births (0 or more), centres (Roskilde or Herlev), and previous larger pelvic surgery (yes/no)). Our secondary analysis for all outcomes will be adjusted for the three stratification variables (see above) and other prognostic variables (history of chronic pelvic pain (yes/no), co-morbidity, enlarging of the abdominal incision to remove uterus (yes/no), multiple adherences or need for other laparoscopic procedures (yes/no). Full analysis will be carried out on both groups, the intention-to-treat population (all randomized participants) and observed cases.

Longitudinal data will be analysed using area under the curve, continuous data will be analysed linear regression, dichotomous data will be analysed using logistic regression, and survival data will be analysed using cox regression. We will perform two sided statistical tests.

We will assess if the thresholds for statistical significance and clinical significance are crossed using the five-point procedure as suggested by Jakobsen et al. [14]. This procedure will include adjustments of thresholds for significance according to the number of primary outcomes (*P*-value threshold 0.033) and number of randomized participants. We will use a Bayes factor threshold for significance of 0.1 based on the prior anticipated intervention effect (see sample size calculation).

We will register if postoperative pathologic examination unexpectedly reveals cancer in a stage indicating further surgery, or if surgery must be converted to open surgery, for other reasons than to remove the uterus. However, we expect such cases to be rare and we will therefore include such participants in the primary analysis. Sensitivity analyses will be performed if the proportion of such cases is larger than expected.

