### Sample size calculation and power estimation

Because our trial is designed with two primary outcomes, our sample size calculation will be based on a type 1 error of 3.3% [15].

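### The primary outcome postoperative pain holds three VAS measures and no named primary variable, while the 0.033 threshold counts pain as one test

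*Protocol article*

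**What the plan says.** All references are to the protocol article.

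- **Primary outcomes.** Pain is scored on a 100 mm VAS "immediately after the operation at the admission to post anaesthesia care unit (PACU) and again" at 5 h, both times with the patient at rest. Then: "Further pain related to physical movements, will be reported in the morning" on days 1 to 3, and only these scores carry the label longitudinal. The paragraph ends: "Postoperative pain will also be related to the analgesics given as we register the use of units of morphine" over the first three days.
- **Statistical analyses.** "Longitudinal data will be analysed using area under the curve"; other continuous data go to linear regression. The threshold procedure includes "adjustments of thresholds for significance according to the number of primary outcomes", giving 0.033, and adds a clinical-significance assessment and a Bayes factor threshold of 0.1 tied to the anticipated effect.
- **Sample size calculation and power estimation.** "Because our trial is designed with two primary outcomes", the type I error is set at 3.3%. The pain calculation uses 10 mm and SD 20 mm for a VAS score with no time point, and arrives at 92 per arm. The trial takes 190 per arm because of SF-36.
- **Data collection.** Pain is scored at 5 h and then on the first three mornings after discharge. No score at PACU admission is mentioned.

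**The concern.** The threshold of 0.033 rests on a count of two primary outcomes, SF-36 physical health and pain, so it allows one test of pain. The definition of pain supplies three candidate variables: a resting score at PACU admission, a resting score at 5 h, and a movement summary for days 1 to 3. Read literally, the first two are separate continuous outcomes for linear regression and the third is an area under the curve.

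Two things are at stake. If the three are tested separately and any of them may support the claim, the false-positive risk exceeds what the threshold was set to give. Even without that, the pain conclusion could depend on which measure is put forward. The Bayes factor has the same gap: its anticipated effect of 10 mm is not attached to any particular pain variable.

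**Working it through.** **1. The plan's own figure.** Inputs from the pain sample size: difference 10 mm, SD 20 mm, two-sided alpha 0.033 ("We will perform two sided statistical tests"), power 90%.

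n per arm = 2 × [SD × (z(1−α/2) + z(1−β)) / difference]² = 2 × [20 × (2.132 + 1.282) / 10]² = 93.2, so 94. The stated 92 agrees within rounding. The planned size therefore belongs to a single test of a single VAS variable at 0.033.

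**2. Number of pain tests.** The label longitudinal is attached to days 1 to 3 only, so the curve rule turns those scores into one variable. The PACU and 5 h scores remain. That makes three. Morphine is not counted.

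**3. False-positive chance, P-value criterion alone.** For independent tests it is 1 − (1 − 0.033)^m:

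- m = 2 (planned: SF-36 and one pain test): 1 − 0.967² = 6.5%
- m = 3 (pain only): 1 − 0.967³ = 9.6%
- m = 4 (SF-36 and three pain tests): 1 − 0.967⁴ = 12.6%

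For correlated tests I simulated multivariate normal statistics (4 million draws, |z| > 2.132). The documents give no correlations, so all of these are assumptions.

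| Correlation among pain tests | Pain, three tests | Trial with SF-36 (correlation 0.2 with pain) |
|---|---|---|
| 0.3 | 9.2% | 12.1% |
| 0.5 | 8.5% | 11.4% |
| 0.7 | 7.4% | 10.3% |
| 0.9 | 5.7% | 8.7% |

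The comparators are 3.3% for one pain test and about 6.5% for the planned two tests.

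**4. Adding the Bayes factor.** Assume it is the likelihood under no effect over the likelihood under the anticipated effect (a point alternative), with 190 per arm, and that it is required in addition to the P-value. The ratio falls below 0.1 when z > d/2 + ln(10)/d, where d is the expected z.

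- Pain: d = 10 / (20 × √(2/190)) = 4.87, so |z| > 2.44 + 0.47 = 2.91.
- SF-36 (4 points, SD 12): d = 3.25, so |z| > 1.62 + 0.71 = 2.33.

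Counting both directions, with pain correlation 0.5 and SF-36 correlation 0.2, any false positive in the trial has a chance of about 2.9% with three pain tests, against 2.3% with one. For pain alone, P(|Z| > 2.91) = 0.36%, and three independent tests give 1 − (1 − 0.0036)³ = 1.1%.

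**5. Two ways out, at 190 per arm.**

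- One named pain variable, 0.033 kept: power for pain = Φ(4.87 − 2.13) = 99.7%.
- Four tests counted, Bonferroni 0.05/4 = 0.0125: SF-36 power = Φ(3.25 − 2.50) = 77.4%, against 86.8% at 0.033.

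**6. Units.** The trapezoid over three mornings, divided by its two-day span, is V1/4 + V2/2 + V3/4, in mm. With a common SD of 20 mm and correlation r between mornings, its variance is 400 × (0.375 + 0.625r), so its SD is at most 20 mm (16.6 mm at r = 0.5).

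**The case against.** The strongest reply is that the article consistently treats pain as one of two primary outcomes and gives a summary for repeated data, so one pain test is a plausible intention. It also announces a separately published analysis plan, which may name the variable. That stands as far as intention goes. It does not settle the text: the curve rule is tied to days 1 to 3 only, and a curve running from PACU to day 3 would join resting to movement scores without the protocol saying so. The article has already fixed a threshold that depends on the answer.

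Three stronger readings are tempting, and the document does not support them:

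- *A significant result on any pain reading is enough.* No sentence says so. It is merely not excluded, and the protocol also lists clinical significance and a Bayes factor. Under the assumptions in step 4, the trial-wide figure drops to about 2.9%. How the Bayes factor is built, and whether it must be met in addition, is not stated here, so that figure is illustrative too.
- *Morphine use is a fourth primary test.* The wording relates pain to analgesics, which reads as context. No effect size or SD is given for morphine.
- *The sample size fails because a curve is measured in mm × days.* This is a matter of scaling. Dividing by the time span restores mm, and 190 per arm is ample.

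Nor are all three measures elicited differently: the PACU and 5 h scores are both at rest and differ only in time.

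**Conclusion.** The point holds in a limited form. The protocol fixes a threshold for one pain test but does not fix the pain variable to which it applies, and its text yields three candidates.

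If these are tested separately at 0.033 and any one may count, the P-value criterion alone gives 5.7% to 9.6% for pain instead of 3.3%. With SF-36 it gives about 11.4% (pain correlation 0.5, SF-36 correlation 0.2) against about 6.5% as planned. These figures rest on assumed correlations and on separate testing, and the further criteria, if binding, would lower them. What remains in any case is that the choice of pain measure is open.

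The schedule conflict adds to this. Mornings after discharge are not postoperative days 1 to 3 when the protocol itself plans on a stay of 40 to 48 h, and length of stay is an outcome on which the arms may differ. The point should be fixed, but it does not invalidate the design.

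**What to change.** Before unblinding:

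1. Name one primary pain variable. One example is the area under the curve of movement VAS over the three mornings, divided by its time span. It is then a mean in mm, and 10 mm / SD 20 mm, 0.033 and the Bayes factor all refer to the same quantity.
2. Make the other VAS readings secondary outcomes.
3. Report morphine use as its own supporting outcome.
4. Reconcile Data collection (5 h, then three mornings after discharge, no PACU score) with Primary outcomes (PACU, 5 h, postoperative days 1 to 3), so that the named variable has one schedule.

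This is a change of wording. All measures are still collected, the threshold stays at 0.033, and pain keeps 99.7% power at 190 per arm. The cost is that only one pain measure can carry the primary claim. Counting every VAS measure as a primary test would cost more, because SF-36 power would fall to about 77%.

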#### Secondary outcomes

Proportion of participants with one or more of the following major complications: organ lesion (injury to bowel, bladder or ureter), vaginal hematoma requiring intravenous AB, vaginal cuff rupture, port hernia, reoperation due to bleeding, deep vein thrombosis, pulmonary emboli or severe cardiac complications and mechanic ileus. *Conversion to laparotomy is categorized as a major complication if done for any other reason than to remove a large uterus. In cases of conversion (mini-laparotomy) to remove a large uterus, mini-laparotomy is not considered a complication, and these patients are pre-operatively informed of the risk of this event.*
Proportion of participants with one or more of the following of minor complications: Cystitis, smaller vaginal cuff hematomas without need for intravenous antibiotics, port infection orpain with normal findings by vaginal ultrasound. All major and minor adverse events will also be assessed separately.The impact of surgery on quality of life, assessed by questionnaire (SF-36-v2, mental health score).Length of hospital stay (hours).Operative time (defined as time from placement of manipulator until last suture).

When calling the participants 6 weeks after their operation, we will also ask the women if and when they returned to work and these reports will be summarized for exploratory purposes.

### Statistical analyses

The statistical analysis plan will be described in detail and published in “BMC Medical Research Methodology”.

Our primary analyses for all outcomes will be adjusted for the three stratification variables (number of previous births (0 or more), centres (Roskilde or Herlev), and previous larger pelvic surgery (yes/no)). Our secondary analysis for all outcomes will be adjusted for the three stratification variables (see above) and other prognostic variables (history of chronic pelvic pain (yes/no), co-morbidity, enlarging of the abdominal incision to remove uterus (yes/no), multiple adherences or need for other laparoscopic procedures (yes/no). Full analysis will be carried out on both groups, the intention-to-treat population (all randomized participants) and observed cases.

Longitudinal data will be analysed using area under the curve, continuous data will be analysed linear regression, dichotomous data will be analysed using logistic regression, and survival data will be analysed using cox regression. We will perform two sided statistical tests.

We will assess if the thresholds for statistical significance and clinical significance are crossed using the five-point procedure as suggested by Jakobsen et al. [14]. This procedure will include adjustments of thresholds for significance according to the number of primary outcomes (*P*-value threshold 0.033) and number of randomized participants. We will use a Bayes factor threshold for significance of 0.1 based on the prior anticipated intervention effect (see sample size calculation).

We will register if postoperative pathologic examination unexpectedly reveals cancer in a stage indicating further surgery, or if surgery must be converted to open surgery, for other reasons than to remove the uterus. However, we expect such cases to be rare and we will therefore include such participants in the primary analysis. Sensitivity analyses will be performed if the proportion of such cases is larger than expected.

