### Data collection

Patients found suitable for participation will be informed about the trial. If the patient wants to participate she will fill out a quality of life questionnaire (SF 36-v2).

*If willing to participate, and after instructions on how to understand the questionnaire the patient completes the SF-36 questionnaire in the preoperative assessment. To reduce risk of bias at the 6 week postoperative telephone interview, patient is re-introduced to and provided with a copy of the SF 36 questionnaire at the time of discharge; further, the research nurse is instructed to stay neutral at the telephone interview* Randomization will be performed in the morning of the operation day. A visual analogue-scale (VAS) for pain scoring will be used when the participants return to the gynaecological unit, 5 h postoperatively. Hospital discharge will be considered when the women are fully mobilized, urinating and pain is controlled with milder oral analgesia. At discharge, use of painkillers stronger than over-the-counter medicine will be registered. The women will be asked to scale their pain at a VAS score in the morning of the first 3 days after discharge. Six weeks after surgery, all patients will receive a telephone call from a nurse, where a SF-36-v2 questionnaire similar to that given preoperatively will be filled out. Pre-operative data is registered by the doctor in the outpatient department record sheet, Operative data by the surgeon in the operation record sheet, and Postoperative data recorded by the nurse surgeon in the discharge department record sheet. Any readmission or complications causing readmission is registered by the doctor in the readmission sheet and will be double-cheeked at the telephone interview. If readmitted or treated at another hospital, this will be registered (linked to personal identification number) at the national patient register where all diagnoses are registered and compiled, with the Hysterectomy Database ensuring no complication will be overlooked.

Time to return to work or other normal life, use of postoperative painkillers, and postoperative complications are noted by the nurse in the telephone interview 6 weeks after the operation (Table 1).

**Table 1 Tab1:** Plan for obtaining data for both 2- and 3D hysterectomies

3D and conventional laparoscopic hysterectomy	Enrolment in outpatient clinic	Allocation and operation	Discharge from hospital	Telephone interview
TIMEPOINT	-t1	0	tx	tx + 6 weeks

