#### SF 36 quality of life

We consider 4 points on the SF 36 quality of life as the minimal relevant difference with a standard deviation of 12 points and we accept a risk of type I error of 3.3% and a risk of type II error of 10%. This results in a sample size of 190 patients in each arm of the trial.

To be able to assess both of the co-primary outcomes, we therefore chose 2 × 190 participants as our necessary sample size.

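### The preoperative SF-36 score is collected but is in neither stated covariate list, so the 6-week SF-36 analysis is valid but gives up precision on the outcome that sets the sample size

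*Protocol article*

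**What the plan says.** All references are to the protocol article.

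- **Data collection:** before surgery, "the patient completes the SF-36 questionnaire in the preoperative assessment". Randomisation follows on the morning of the operation, so this is a true pre-randomisation baseline. Table 1 lists SF-36 among the baseline variables.
- **Primary outcomes:** the first co-primary outcome is "The impact of surgery on quality of life, assessed by questionnaire (SF-36-v2, physical health score") by telephone at 6 weeks. The mental health score is a secondary outcome.
- **Statistical analyses:** continuous outcomes are analysed by linear regression. "Our primary analyses for all outcomes will be adjusted for the three stratification variables", namely parity, centre and previous pelvic surgery. The secondary analysis adds chronic pelvic pain, co-morbidity, enlargement of the incision, and adhesions or other laparoscopic procedures. Baseline SF-36 is in neither list. The section also states: "We will perform two sided statistical tests".
- **SF 36 quality of life (sample size):** "We consider 4 points on the SF 36 quality of life as the minimal relevant difference with a standard deviation of 12 points", with "a risk of type I error of 3.3% and a risk of type II error of 10" per cent. The result is given as 190 per arm, which becomes the trial's sample size. The abstract plans 400 women, which is 200 per arm.

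**The concern.** The same questionnaire is administered before surgery and at 6 weeks, and the outcome is described as the impact of surgery. Yet the preoperative score has no stated role in the analysis. The secondary list has room for events known only at operation, such as an enlarged incision, but not for the pre-randomisation measurement of the outcome itself.

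In a linear model, a baseline that correlates r with the outcome reduces the residual variance by the factor 1 − r². It also takes chance baseline differences between the arms out of the estimate. SF-36 is the outcome where this matters most: it sets the sample size, and its power is below the stated 90% on the protocol's own inputs.

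**Working it through.** **Inputs from the protocol.** Difference 4 points, SD 12 points, type I error 0.033, two-sided, power 90%, allocation 1:1, 190 per arm stated, 400 women in the abstract.

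**Assumptions.** The protocol gives no correlation r between the preoperative and 6-week scores, so a range is shown. It does not say whether 12 is the SD of the 6-week score, of a change score or of a residual; the first is assumed.

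**Step 1: the stated sample size.**

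n per arm = 2 × SD² × (z₁₋α/₂ + z₁₋β)² / difference²

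- At alpha 0.033: z = 2.132 and 1.282. n = 2 × 144 × (3.4136)² / 16 = 18 × 11.653 = 209.8, so **210 per arm** (211 with the t distribution).
- At alpha 0.05: n = 18 × (1.960 + 1.282)² = 189.1, so 190 per arm.

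The stated 190 therefore does not follow from 3.3%; it is the figure for two-sided 5%. The pain calculation, by contrast, roughly reproduces at 3.3% (94 computed, 92 stated).

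**Step 2: power without the baseline.**

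Power = Φ(4 / (12 × √(2/n)) − 2.132)

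- n = 190: standard error 12 × √(2/190) = 1.231; 4/1.231 = 3.249; Φ(1.117) = **86.8%**.
- n = 200: standard error 1.200; 4/1.200 = 3.333; Φ(1.201) = **88.5%**.

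**Step 3: power with the baseline.** Replace 12 by 12 × √(1 − r²). The sample size for 90% power becomes 209.75 × (1 − r²), rounded up.

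| Assumed r | Residual SD | Power at 190 per arm | n per arm for 90% |
|---|---|---|---|
| 0 | 12.00 | 86.8% | 210 |
| 0.1 | 11.94 | 87.1% | 208 |
| 0.2 | 11.76 | 88.2% | 202 |
| 0.3 | 11.45 | 89.9% | 191 |
| 0.4 | 11.00 | 92.1% | 177 |
| 0.5 | 10.39 | 94.7% | 158 |
| 0.6 | 9.60 | 97.3% | 135 |
| 0.7 | 8.57 | 99.2% | 107 |

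**Step 4: the correlation needed for 90%.** Set 4 / (12 × √(1 − r²) × √(2/n)) = 3.4136 and solve for r.

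- n = 190: √(1 − r²) = 3.249/3.4136 = 0.952, so r ≈ **0.31**.
- n = 200: √(1 − r²) = 3.333/3.4136 = 0.976, so r ≈ **0.22**.
- n = 171 (190 less an assumed 10% loss): r ≈ 0.43.

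**The case against.** The strongest objection is that nothing here is an error. Linear regression adjusted for the stratification variables is valid for a randomised comparison: the estimate is unbiased and the type I error is controlled. One covariate set for every outcome is a coherent choice. This stands, and the point is therefore about precision only. A reader might infer from the omission that the planned SF-36 comparison is biased; the protocol does not support that, because chance imbalance under randomisation is already reflected in the standard error.

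A second objection is that a detailed statistical analysis plan is announced and not shown, and that it could add the baseline score or define the endpoint as a change. This has some force, since the wording of the outcome leaves raw score or change open. But the protocol does not leave the covariates to that plan. It lists them for all outcomes, so an analysis plan that added the baseline would depart from the published primary model.

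Third, a reader might infer that adding the baseline would by itself restore the missing power. The protocol does not support this either. It gives no correlation, and r = 0.3 falls just short at 190 per arm. If 12 is already a change-score or residual SD, the gain is smaller than tabulated. If 400 women are recruited and analysed, the shortfall is about 1.5 points (90 − 88.5), not 3.2 (90 − 86.8).

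Finally, the shortfall arises in the sample-size section. It is a separate defect and should not be counted again here.

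**Conclusion.** The point holds as a recommendation on precision. A baseline measurement of a co-primary outcome is collected before randomisation and left out of both covariate lists that the protocol fixes. The analysis as written is valid but less efficient than the collected data allow.

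If SD 12 refers to the 6-week score, the baseline could recover 90% power when r is at least about 0.31 with 190 analysed per arm, or about 0.22 with 200. Below those values it narrows the gap without closing it. The size of the gain rests on an assumed r and on that reading of the SD. The recommendation does not: a prespecified pre-randomisation covariate keeps the comparison valid and costs one degree of freedom even if r is low.

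**What to change.** Before unblinding, specify the primary SF-36 analysis as linear regression of the 6-week physical health score on arm, the three stratification variables and the baseline physical health score. Specify the mental health score in the same way, with its own baseline. Include the baseline scores in any multiple imputation model. State whether the SD of 12 is that of the 6-week score, the change or a residual.

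The cost is one covariate per SF-36 model and a documented change to the published covariate list; no new data are needed.

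The covariate does not repair the sample-size statement. The figure of 190 per arm, against 210 from its own inputs, needs its own correction in the SF 36 quality of life section.

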### Interventions

In order to assess which mode of laparoscopy is more favourable in a RCT, it is necessary to use similar and well-defined procedures in all other areas around the surgery. Therefore the preoperative information and patient education is standardized. Pre-emptive medication is 8 mg dexamethasone, 2 g paracetamol, 400 mg Ibumetin and 4 mg Ondacetron. Anaesthesia and postoperative care is also standardized as well as the operative procedure.

Standard preoperative assessment will be performed together with transvaginal ultrasound estimating the size of the uterus. Operative procedures will follow the previously described “Gold standard” as follows: A manipulator will be used in all patients to expose and delineate different anatomical structures. For ligation and dissection, a Thunderbeat® bipolar/ultrasound sealing and cutting energy device will be used. After detachment, uterus will be removed through the vaginal vault. In case of a very narrow vagina combined with a myomatous uterus it may be necessary to enlarge the abdominal incision [13]. Morcellation or any other destruction of the uterus inside the abdomen will not be performed. The vaginal vault will be closed laparoscopically with a running Vicryl 2–0 suture or a barbed suture V-lock® 2–0. Urinary catheter will be removed immediately after the operation. For postoperative pain relief, the patients will be given sufentanil/Fentanyl in the recovery ward, and paracetamol, NSAID and in some cases morphine in the gynaecological unit. After a few hours on the recovery ward, they will return to the gynaecological unit.

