Baseline variables: height, weight, age, prior operations, chronic pain, parity, estimated weight of uterus, indication for operation, site. Quality of life by SF-36 questionnaire	x	x		
Outcome variables 1: operating time, bleeding, concomitant surgery, weight of uterus		x		
Outcome variables 2: Postoperative pain and medication	x		x	
Outcome variables 3: re-admissions, complications at home, return to work, pain, return to daily living, unexpected malignancy. Quality of life by SF-36 questionnaire	x			x

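### The secondary adjusted analysis of every outcome includes covariates that arise or are recorded during surgery, after randomisation, so it may not estimate the total effect of 3D laparoscopy

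*Protocol article*

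**What the plan says.** The Statistical analyses section sets out two adjusted models for each outcome. For the first: "Our primary analyses for all outcomes will be adjusted for the three stratification variables", that is, parity, centre and earlier major pelvic surgery. For the second: "Our secondary analysis for all outcomes will be adjusted for the three stratification variables (see above) and other prognostic variables". Those further variables are a history of chronic pelvic pain, co-morbidity, and "enlarging of the abdominal incision to remove uterus (yes/no), multiple adherences or need for other laparoscopic procedures (yes/no".

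Other sections fix the timing and the recorder:

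- Data collection: "Randomization will be performed in the morning of the operation day".
- Interventions, describing removal of the uterus once it is detached: "In case of a very narrow vagina combined with a myomatous uterus it may be necessary to enlarge the abdominal incision".
- Blinding: "The surgeon operating the patient cannot, for obvious reasons, be blinded".
- Data collection, on who records: "Operative data by the surgeon in the operation record sheet".
- Table 1: "Baseline variables: height, weight, age, prior operations, chronic pain, parity, estimated weight of uterus, indication for operation, site". Neither incision enlargement nor adhesions nor additional procedures is in that list. Concomitant surgery is in the next row, among outcome variables collected at operation.

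**The concern.** A covariate-adjusted estimate in a randomised trial keeps its causal meaning when the covariates are fixed before allocation. Incision enlargement, and the combined item for adhesions or additional procedures, become known only in the operating theatre, when the arm is already in use and known to the person recording. The Background section expects 3D to work through better imaging and through faster, safer surgery. On that hypothesis, what happens during the operation may lie on the path from treatment to pain, quality of life, operative time, stay and complications.

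Adjusting for such an item can do two things. It can remove the part of the effect that runs through the item. It can also create an imbalance in unmeasured surgical difficulty between arms within levels of the item.

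The model covers both co-primary outcomes and every secondary outcome. If it disagreed with the primary analysis, a reader could take it for the better-controlled result, because its covariates are described as prognostic.

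**Working it through.** **Timing of each covariate, from the protocol's own text**

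| Covariate | When known | Can the arm affect it? |
|---|---|---|
| Chronic pelvic pain (history) | before randomisation | no |
| Co-morbidity | before randomisation, if taken pre-operatively | no |
| Incision enlargement | at removal of the uterus | possibly |
| Additional laparoscopic procedures | during surgery, unless planned | possibly |
| Adhesions | present beforehand, seen and recorded at surgery | presence no; detection and recording possibly |

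The last two share one yes/no item, so the part that treatment may affect cannot be separated from the anatomical part.

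**Size, by illustration.** The protocol gives no frequency or effect for these items, so every rate and coefficient here is an assumption. Let A = 1 for 3D. Let M be incision enlargement, with proportions p2 (conventional) and p3 (3D). Let U be unmeasured difficulty, standard normal, with correlation r to the latent variable that determines M. The outcome is

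Y = d·A + bM·M + bU·U + error.

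In large samples, linear regression gives:

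- without M: d + bM·(p3 - p2), the total effect;
- with M: d - bU·g·(p3 - p2), where g = r·(f2 + f3) / [p2(1 - p2) + p3(1 - p3)] and f2, f3 are standard normal densities at the two thresholds.

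*Pain (mm VAS).* Assume d = 0, bM = +15, r = 0.5. For 20% v 10%, f2 = 0.2800 and f3 = 0.1755, so g = 0.5 × 0.4555 / (0.16 + 0.09) = 0.911. The total effect is 15 × (-0.10) = -1.50. With bU = +5 (difficulty raises pain), the adjusted effect is 5 × 0.911 × 0.10 = +0.46.

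| Enlargement, conventional v 3D | bU | Total | Adjusted |
|---|---|---|---|
| 15% v 10% | +5 | -0.75 | +0.23 |
| 20% v 10% | +5 | -1.50 | +0.46 |
| 30% v 15% | +5 | -2.25 | +0.65 |
| 20% v 10% | 0 | -1.50 | 0.00 |
| 20% v 10% | -5 | -1.50 | -0.46 |
| 20% v 20% | +5 | 0.00 | 0.00 |

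Simulation of 2 million patients agrees: -1.50 and +0.46 for 20% v 10% with bU = +5.

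*SF-36-type score.* Assume bM = -10, bU = -6, r = 0.6, and 20% v 10%. Then g = 0.6 × 0.4555 / 0.25 = 1.093. With d = 0, the total is +1.0 and the adjusted effect is -6 × 1.093 × 0.10 = -0.66. With d = +2, they are +3.0 and +1.34.

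**Scale.** In the 20% v 10% pain case with bU = +5, adjustment moves the estimate by 0.46 + 1.50 = 1.96 mm. With the protocol's SD of 20 mm and 190 per arm, the standard error of the difference is 20 × √(2/190) = 2.05 mm. The shift is thus about one standard error, and about a fifth of the 10 mm minimal relevant difference. For the SF-36 case the shift is 1.0 + 0.66 = 1.66 points, against a standard error of 12 × √(2/190) = 1.23 and a minimal relevant difference of 4 points.

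**The case against.** The best defence has four parts.

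**The model is secondary.** The primary analyses adjust only for variables known before randomisation. This stands. A reader might infer that the trial's randomised comparison is compromised; the documents do not support that, because the main estimates do not use these covariates.

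**There may be no effect of 3D on the items.** The Interventions section attributes enlargement to a narrow vagina with a myomatous uterus, which is anatomy rather than vision, and the protocol nowhere predicts fewer enlargements with 3D. This also stands as a limit: with equal rates the table shows no bias. It does not rescue the choice, because the plan has no means of ensuring equal rates.

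**Adhesions are pre-existing, and some additional procedures may be planned.** This is correct, and it weakens the point for adhesions. What enters the model, however, is what an unblinded surgeon sees and records, in a joint item with additional procedures. The Table 1 evidence should not be overread either: the row that holds concomitant surgery also holds uterus weight, so its heading may partly reflect when data are collected. Even so, it puts concomitant surgery outside the baseline list.

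**The illustrated effects are small and assumed.** This is true. Reversal also needs difficulty to worsen the outcome; if difficulty lowered pain, the same inputs give attenuation only (-1.50 to -0.46 mm).

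One further inference should be avoided. The Primary outcomes section says pain will be related to analgesic use, but it does not make morphine a covariate in the pain model.

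**Conclusion.** The point holds for the secondary adjusted analysis only. As written, that analysis conditions on items that arise or are recorded after allocation and that treatment may affect. Its estimate then need not be the total effect of 3D against conventional laparoscopy, and the protocol does not present it as a direct-effect or mediation analysis.

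The case is strongest for incision enlargement and additional procedures. It is sharpest for operative time, which runs from manipulator placement to the last suture and so includes the time these steps take. It is weaker for adhesions.

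Size cannot be derived from the protocol. Under the assumed inputs, a total effect of -1.5 mm VAS becomes about +0.5 mm; other assumptions give attenuation to zero, partial attenuation, or no change. A reader might infer that the adjusted results will have the wrong sign. The documents support only that they can, on two conditions: the arms differ on these items, and difficulty worsens the outcome.

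**What to change.** In the Statistical analyses section, limit the secondary adjustment set to variables fixed before randomisation: the stratification variables, chronic pelvic pain and pre-operative co-morbidity. Table 1 does not name co-morbidity among its baseline variables, so state that it is taken from the pre-operative record. Baseline variables already collected, such as ultrasound-estimated uterus weight and baseline SF-36, could be added; that is optional.

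Report incision enlargement, adhesions and additional procedures by arm, either descriptively or in an analysis labelled exploratory. Adhesions and additional procedures should be separate items there.

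The cost is a sentence or two in the analysis section. The optional covariates are already collected, and neither the primary analyses nor the sample size changes. Separating the combined item needs only that the operation record sheet keeps its two parts apart.
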